## Discussion

The DIATEMP trial is a multicenter RCT with the aim to determine cost-effectiveness and cost-utility of at-home monitoring of plantar foot temperature for preventing foot ulcer recurrence in high-risk diabetes patients. Following three successful RCTs demonstrating the efficacy of at-home foot temperature for preventing diabetic foot ulcer recurrence in one geographical region (Texas) in the US [15–17], this is the first adequately designed and powered RCT to investigate this intervention in another geographical location (the Netherlands). In addition to the previous RCTs, we include assessment of cost-effectiveness and cost-utility. After the start of participant inclusion in the study, we modified and improved our protocol to a limited extent based on new insights and necessities; the most important changes are described and clarified below.

Crucial in any trial is sufficient patient recruitment. We anticipated, based on calculations of recruitment rate from a previous trial [24], that the required period for including the 304 participants would take 15 months in the participating five centers. Unfortunately, the response rate of potentially eligible participants was below 25%, while we hypothesized a response rate of approximately 50%. To increase participant inclusion, we intensified the collaboration with the study centers and the involved podiatrists, and we added two more study centers (VU Medical Center, Amsterdam, and Medisch Spectrum Twente, Enschede). We additionally adjusted one of the inclusion criteria. We initially included only participants with a healed foot ulcer in the 2 years prior to study randomization. This had the advantage of selecting only the highest-risk patients, with re-ulceration rates being approximately 60% in the first 3 years after healing [1]. To increase the potential for inclusion we prolonged the ulcer-free period before study randomization to a maximum of 4 years. These changes in the protocol resulted in increased recruitment rates for the trial.

Due to the high risk of ulceration and frequent occurrence, diabetic patients with a history of amputation are important to include in a prevention trial [2]. In the trial of Lavery and colleagues, patients with a minor amputation, such as a great toe, were instructed to measure their foot temperature at the basis of the amputated region, while patients with an amputation proximal of the forefoot were excluded [17]. Other trials on at-home monitoring of skin temperature describe no specific protocol for patients with an amputation [15, 16, 19]. Since at-home foot temperature monitoring is based on the principle of comparing bilateral foot temperatures at the same anatomical region, a specific protocol is needed for participants with an amputation. Initially, we used the protocol of Lavery and colleagues as described above; however, this often resulted in participants finding temperature differences that were consistently above 1.5 °C in the first 2 weeks of monitoring, increasing the potential for false-positive outcomes. These high temperature differences occur due to the changed anatomy and biomechanics following amputation, with tissue stress and temperature being structurally higher at the stump location. We modified our measurement protocol to take such systematic differences into account, as described in the methodology. Consequently, only participants with a bilateral amputation proximal to the Chopart joint had to be excluded from participation in the trial.

The measurement protocol in our trial was largely based on previous trials of Lavery and Armstrong and colleagues, in which six predefined regions of interest were measured: hallux, first, third, and fifth metatarsal heads, midfoot, and hindfoot [15–17]. Since many foot ulcers occur at the toes, and re-ulceration occurs mostly at the previous ulcer location [31], we added the option of measuring a maximum of two regions of interest in addition to the standard six, to provide a solution for previous foot ulcers or signs of pre-ulceration (e.g., abundant callus, subcutaneous hemorrhage or blister) being present at toes two to five. During the trial we noticed (blinded to group allocation) that ulcers did not develop at the midfoot or hindfoot. Therefore, in October 2017, we modified the six standard regions of interest to include the plantar surface of the second and third toes instead of the midfoot and hindfoot [20, 24]. For participants with a high risk of developing a foot ulcer at the midfoot or hindfoot, such as in midfoot Charcot deformity, this region would still be selected for temperature measurement as an additional region of interest.

A strength of this trial is that, in addition to assessing effectiveness in preventing foot ulcer recurrence, we assess cost-effectiveness and cost-utility of the procedure. These outcomes are important given the extra investment in measurement equipment and time of the health care professional and the patient in monitoring the foot. Another strength is that not just any foot ulcer, but only plantar foot ulcers and ulcers that develop at the apex of the toes, the interdigital spaces, and the lateral and medial forefoot are the primary clinical outcome. These locations are often subject to foot ulceration as a result of repetitive mechanical stress due to deformity present and rubbing of the toes. If inflammation occurs at these areas before foot ulceration develops, we anticipate that the temperature increase due to the inflammation is being measured at one of the measurement locations on the foot.

In conclusion, the DIATEMP trial aims to provide level-1 evidence for the effectiveness, cost-effectiveness and cost-utility of at-home monitoring of foot skin temperature to prevent foot ulcer recurrence in high-risk diabetes patients. The outcomes of this RCT, together with analyses on the usability and implementability of the intervention, is expected to have impact on the use of foot temperature monitoring and the design of foot temperature monitoring systems as method for self-management to prevent diabetic foot complications in high-risk patients with diabetes.

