## Background

Despite many recent advances in medical therapies, the prevalence of diabetes mellitus and diabetes-related complications continues to increase. With a life-time prevalence of 19–34% [1], foot ulceration is one of the most common complications in people with diabetes. This frequently leads to hospitalization and lower-extremity amputation [2]. With an annual incidence rate of 2.2% and one million people with diabetes, approximately 22,000 ulcers develop in the Netherlands each year [3, 4]. Foot ulcers frequently become infected, cause great morbidity and have a negative impact on health-related quality of life and patient mobility [5–7]. Furthermore, mortality risk at 10 years is twice as high in patients who had a foot ulcer compared to those who have not [8]. Besides the patient and social burden of diabetic foot disease, foot ulcers cost €5000 to €17,000 per episode in specialized centers in Europe and place a large burden on the health care systems [9].

Recognizing the potential for severe morbidity and high treatment costs related to foot ulceration, many experts call for widespread establishment of preventative foot care programs for persons with diabetes [10–12]. The most common mechanism of foot ulceration involves a cumulative effect of repetitive trauma at pressure points on the foot over the course of several days that goes unrecognized because of the presence of neuropathy [1]. Guidelines therefore recommend proper patient education, identification and treatment of the diabetic foot at-risk, integrated foot care and protective pressure-relieving footwear [10, 13, 14]*.* Despite these guidelines, the incidence of foot ulcer recurrence remains very high: 40% in the first year and 60% in the first 3 years after healing of a foot ulcer [1]. Therefore, care providers and patients are in need of new adjunctive ways to prevent ulcer recurrence.

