### Sample size calculation

Based on the results of a footwear efficacy trial that was largely conducted in the same centers as this trial and also assessed patients with a history of foot ulceration [24], we anticipate for the usual-care group that 44% of participants will develop a recurrent foot ulcer during 18 months’ follow-up. Using a conservative estimate from three previous trials on the effectiveness of at-home foot temperature monitoring [15–17], we anticipate that 28.6% of participants in the enhanced therapy group will develop a recurrent foot ulcer in 18 months; this represents a 35% effect size. With α = 0.05 (two-sided), power 80%, and based on an intention-to-treat analysis in which clinical outcome data from all included patients will be assessed, 304 eligible participants are required and will be randomly assigned.

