### Randomization and blinding

After the baseline assessment, participants will be randomly assigned to either usual care or enhanced therapy using an online-accessible, computer-generated allocation sequence (TENALEA Clinical Trial Data Management System; National Cancer Institute, Amsterdam, The Netherlands) that uses the nondeterministic minimization method. The allocation sequence will be prepared and managed by a noninvolved investigator from the Clinical Research Unit of the Academic Medical Center in Amsterdam. Randomization will be stratified according to participating center and gender.

The persons responsible for assessing the primary clinical outcome (i.e., foot ulcer) will be blinded to the group allocation. Participants are asked not to disclose their allocation in the study to their treating physician. The involved podiatrists and investigators are not blinded to group allocation.

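### Time since ulcer healing, the only prognostic gradient the article quantifies, enters neither the minimization nor the named ulcer comparisons; this costs a little precision and causes no bias

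*Protocol article*

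**What the plan says.** All references are to the protocol article; no separate analysis plan is shown.

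- **Risk over time.** The Background gives recurrence as "40% in the first year and 60% in the first 3 years after healing of a foot ulcer".
- **Eligibility.** The Discussion reports that the trial first required an ulcer healed in the 2 years before randomization, describes that window as picking out the patients at highest risk, and says of the later change: "we prolonged the ulcer-free period before study randomization to a maximum of 4 years". Under Inclusion and exclusion criteria, a confirmed midfoot or forefoot Charcot diagnosis is an alternative route of entry.
- **Allocation.** Nondeterministic minimization is used: "Randomization will be stratified according to participating center and gender".
- **Comparisons.** Statistical analysis names a chi-square test for effectiveness and a competing risk analysis for time to ulcer. No covariate is named for either. The one subgroup named under Economic evaluation is level of adherence to monitoring.
- **Size.** "we anticipate for the usual-care group that 44% of participants will develop a recurrent foot ulcer during 18 months’ follow-up"; "we anticipate that 28.6% of participants in the enhanced therapy group will develop a recurrent foot ulcer in 18 months"; and "304 eligible participants are required and will be randomly assigned".

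**The concern.** When a baseline variable predicts the outcome, putting it in the comparison sharpens the estimate at little cost. Here the variable is part of the eligibility rule, and the article's own figures show risk falling after the first year. Yet the named effectiveness test takes no covariate.

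There is also a descriptive side. The primary outcomes are economic, and the monitoring outlay per prevented ulcer depends on absolute risk. A single pooled ratio hides the mix of risks behind it. The one planned subgroup cannot show this, because adherence to monitoring arises after randomization and exists only in the enhanced therapy group.

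**Working it through.** **1. The plan's own figure.** Inputs from Sample size calculation: 44% against 28.6%, two-sided alpha 0.05, power 80%; 1:1 allocation is assumed. With pooled proportion 0.363 and difference 0.154:

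n per arm = [1.96 × √(2 × 0.363 × 0.637) + 0.842 × √(0.44 × 0.56 + 0.286 × 0.714)]² / 0.154² = 151.9, so 152 per arm and 304 in total. This matches.

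SE of the risk difference = √((0.2464 + 0.2042)/152) = 5.44 points; 95% half-width 1.96 × 5.44 = 10.7 points.

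**2. Risk by time since healing.** Inputs: 40% by 1 year and 60% by 3 years (Background). Assumption: the hazard is constant within year 1 and within years 2 to 3.

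- Year 1: −ln(0.60) = 0.511 per year.
- Years 2 to 3: ln(0.60/0.40)/2 = 0.203 per year.

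The 18-month risk for a patient healed a years ago and still ulcer-free is 1 − S(a + 1.5)/S(a):

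| Healed before entry | 18-month risk |
|---|---|
| just healed | 45.8% |
| 6 months | 36.8% |
| 1 year | 26.2% |
| 18 months | 26.2% |

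Beyond 18 months since healing, the 18-month window runs past year 3, where the article gives no figure; 26.2% is then an extrapolation. With healing times spread evenly over the first year (assumed), the mean risk is 36.5%.

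**3. Chance imbalance.** If half of each arm healed more than a year ago (assumed), the between-arm difference in that share has SD √(2 × 0.25/152) = 5.74 points. The resulting shift in the risk difference is that SD times the risk gap between strata, using the usual-care gap for both arms:

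| Gap | SD of shift | 1.96 SD | Share of variance |
|---|---|---|---|
| 36.5 − 26.2 = 10.3 points (even spread over year 1) | 0.59 points | 1.2 points | (0.59/5.44)² = 1.2% |
| 45.8 − 26.2 = 19.6 points (all recent healers just healed) | 1.12 points | 2.2 points | (1.12/5.44)² = 4.2% |

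With a 20% share the SD of the imbalance is 4.59 points, and the variance shares fall to about 0.8% and 2.7%.

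**4. Power.** If adjustment removes a fraction f of the variance, power ≈ Φ(2.80/√(1 − f) − 1.96). For f = 1.2% this is 80.5%; for f = 4.2% it is 81.7%. Simulation of the wider gap (200,000 trials per setting, control rate averaging 44%) agrees: the unadjusted test has 80.1 to 80.2% power, and the Cochran-Mantel-Haenszel test stratified by time since healing has 81.1 to 81.7%.

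**5. Validity without adjustment.** In the same simulations with no treatment effect, the mean difference was 0.00 to 0.01 points. Type I error was 5.0 to 5.3% unadjusted and 5.0 to 5.1% stratified.

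**6. Is the widening the source?** With entry spread evenly within each window and the hazard extrapolated, the mean 18-month risk is 31.4% for patients healed 0 to 2 years ago and 26.2% for 2 to 4 years. Stratifying at 2 years would remove only 0.2 to 0.3% of the variance.

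**7. Absolute benefit.** Assuming the planned 35% relative reduction is constant, 45.8% gives 16.0 points, or about 6.2 patients monitored per ulcer prevented. At 26.2% it is 9.2 points, or about 10.9 patients. The ratio is about 1.75 at this extreme and 31.4/26.2 = 1.2 for the 2-year split.

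**The case against.** The strongest reply is that nothing in the plan is invalid. Both arms are recruited concurrently under the same criterion, so chance imbalance in healing time is ordinary random error already counted in the standard error. That stands in full. A reader might infer that an imbalance contaminates the treatment effect, but steps 3 and 5 show no bias. Even the extreme 2.2-point shift lies well within a half-width of 10.7 points, and it gives day-of-healing risk to half of each arm.

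A reader might also infer that the move from 2 to 4 years created the problem. On the article's figures the hazard drop comes at 1 year, inside the original window, and no 18-month risk is given for the patients who were added. Nor can time since healing be called the strongest risk factor: it is the only one with numbers, and the article ranks none.

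Finally, covariates are commonly left to an analysis plan, and a journal article condenses. That limits the point to the comparisons this article names. It does not remove it, because the article fixes a chi-square test, which takes no covariate. Whether 44% still describes the widened population is a separate question on which this point makes no claim.

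**Conclusion.** A minor point on efficiency and reporting. Time since healing is the only quantified prognostic gradient in the article and is absent from both the minimization and the named ulcer comparisons. The cost is about 1 to 4% of the variance of the risk difference, or roughly 0.5 to 1.6 points of power, with no bias and no inflation of type I error. This rests on a piecewise-constant hazard extrapolated past year 3, on 1:1 allocation, and on about half of each arm having healed more than a year ago; the article does not report that share. The upper end needs all recent healers to have healed just before randomization. If few patients healed recently, the gain is smaller still. The descriptive argument is the better reason to act: absolute risk drives the cost per prevented ulcer, and no planned subgroup describes it by a baseline characteristic.

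**What to change.** Before analysis, pre-specify time since healing as a covariate or stratum in the ulcer comparison and in the incremental cost and effect estimates behind the bootstrap. Use it as continuous, or as 1 year or less against more than 1 year; the cut belongs at 1 year because that is where the article's figures place the change. Give entrants on Charcot diagnosis alone their own category, since they may have no healing date.

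Also report, descriptively, event rates, risk difference and incremental cost for patients who met the original 2-year criterion and for those admitted only under the 4-year one. State that these estimates will be imprecise, because 304 patients give 80% power for the whole population only.

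No change to allocation is proposed: recruitment was expected to end in July 2018, before the article appeared in September 2018.

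The cost is one covariate and one table. Ulcer history is recorded at baseline, but the article does not say that the healing date itself is captured; this should be confirmed.

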## Trial status

Netherlands Trial Registry, ID: NTR5403. Registered on 8 September 2015. The trial commenced recruitment in November 2015 and recruitment is expected to be completed in July 2018.

## Abbreviations

BIA: Budget impact analysis
CRF: Case Report Form
DIATEMP: Diabetic Foot Temperature Trial
EQ-5D-3 L: 3-Level EuroQol Quality of Life Scale
iMCQ: Medical Consumption Questionnaire
iMTA: Institute for Medical Technology Assessment
iPCQ: Productivity Cost Questionnaire
ISPOR: International Society for Pharmacoeconomics and Outcomes Research
IWGDF: International Working Group on the Diabetic Foot
METC: Medical Research Ethics Committee; in Dutch: Medisch Ethische Toetsings Commissie
PAD: Peripheral arterial disease
PEDIS classification: Perfusion, Extent, Depth, Infection, and Sensation classification
QALY: Quality-adjusted life year
RCT: Randomized controlled trial
SAE: Serious adverse events
SF-36: 36-Item Short Form Health Survey
SPIRIT: Standard Protocol Items: Recommendations for Interventional Trials
